#### Timeline

Figure 2 shows the timeline of the trial. We started recruitment in April 2013 and will end recruitment of Veterans in September 2015. We are currently undergoing recruitment of surrogate participants and expect to complete recruitment in September 2016.

**Fig. 2 Fig2:**
[figure not shown]
PREPARE Study Timeline

### Data analysis

#### RCT efficacy analysis

Our primary analyses will compare advance directive completion rates and change in engagement in the five ACP behaviors (see Primary outcome section) using behavior change measure scores on a 5-point Likert scale (analyzed as average Likert scores and total scores of 57 to 285) and action measure scores using yes and no responses (scores 0 to 25) from baseline to 1 week, and 3, and 6 months between study arms. We first will use means, medians, and ranges to describe continuous variables, and we will use proportions to describe categorical and dichotomous variables. Baseline comparability of the two groups will then be assessed using t-tests for continuous variables and chi-square tests for proportions. To examine the outcomes between the two study arms longitudinally, we will use mixed effects linear, Poisson, or negative binomial regression for continuous outcome measures and mixed effects logistic regression for dichotomous measures. The mixed effects models will include a random effect for subjects and fixed effects for the primary modeling terms of time, study arm, and an interaction term of study arm and time. We will treat the time variable in three different ways: (i) our first model will encode the time variable as a dummy variable for baseline versus the post-intervention time points; (ii) we will next model time in a continuous linear fashion; (iii) we will lastly consider an arbitrary time course by treating time as a categorical factor variable. We will also adjust for the randomization blocking factors of health literacy (limited versus adequate) and race (white versus non-white) [39] and for any predictor variables that differ between study arms at baseline. We will also include random physician intercepts to account for nesting of patients within physicians. We will consider including random effects for the primary modeling terms of time, study arm, and their interaction. Modeling decisions (for example, which mean structure to use and which random effects to include) will be based on comparing values of the Akaike Information Criterion. Models will be fit using the xt routines in Stata. Mediation analyses will use Stata’s mediation package, which allows estimation of the average causal mediation effect using a potential outcomes framework with either continuous or binary outcomes and allows for sensitivity analyses with respect to violation of the sequential ignorability assumption [40]. Moderating variables will be tested with interaction terms.

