**Methods/Design:**

This randomized controlled trial with blinded outcome assessment is designed to determine the efficacy of PREPARE to engage older Veterans in the ACP process. Veterans who are ≥ 60 years of age, have ≥ two medical conditions, and have seen a primary care physician ≥ two times in the last year are being randomized to one of two study arms. The PREPARE study arm reviews the PREPARE website and an easy-to-read advance directive. The control arm only reviews the advance directive. The primary outcome is documentation of an advance directive and ACP discussions. Other clinically important outcomes using validated surveys include ACP behavior change process measures (knowledge, contemplation, self-efficacy, and readiness) and a full range of ACP action measures (identifying a surrogate, identifying values and goals, choosing leeway or flexibility for the surrogate, communicating with clinicians and surrogates, and documenting one’s wishes). We will also assess satisfaction with decision-making and Veteran activation within primary care visits by direct audio recording. To examine the outcomes at 1 week, 3 months, and 6 months between the two study arms, we will use mixed effects linear, Poisson, or negative binomial regression and mixed effects logistic regression.

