### Aims and primary hypotheses

The primary hypothesis of this study is that older Veterans randomized to the PREPARE arm (the PREPARE website plus the easy-to-read advance directive), compared to the control arm (the easy-to-read advance directive alone), will have increased rates of ACP documentation in their medical record (advance directives, clinicians notes, code status orders). Because this is the standard outcome measure for advance care planning, it is the outcome on which we calculated our sample size (see Sample Size Section). However, ACP consists of several behavioral processes (knowledge, contemplation, self-efficacy, and readiness) for several discrete ACP behaviors, including identifying surrogates, identifying values, and communicating this information with clinicians, surrogates, and other loved ones. Therefore, we feel our secondary outcomes and hypotheses are just as clinically meaningful. The secondary hypotheses of this study are that older Veterans randomized to the PREPARE arm, compared to the control arm, will have greater engagement in ACP including behavior change process measures and additional ACP actions beyond advance directive documentation as measured by a validated survey [22]. Secondary hypotheses also include greater Veteran activation and clinician responsiveness within the clinical encounter as measured by audio-recording a subset of clinical visits, Veteran satisfaction with clinician communication, Veteran engagement and satisfaction with decision-making, surrogate-reports of Veteran engagement in ACP behaviors, and fewer reported barriers to ACP for the PREPARE versus control arm. Other outcomes include comparisons of acceptability and usability of the PREPARE website plus an easy-to-read advance directive versus an advance directive alone (Table 2).

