Functional status	Activities of Daily Living (ADL) and Instrumental Activities of Daily Living (IADL)	15	Morbidity/mortality correlation [51, 52]		X			
Self-rated health status	In general how would you rate your health? (5-pt Likert)	1	Correlation with global health, spearman’s rho = -63, and mortality [53]	X				
Self-rated quality of life	In general, how would you rate your overall quality of life in the past week (5-pt Likert)	1	Test-retest coefficient = 0.81 [54]	X				
Comorbid illness	Determined by ICD-9 codes (chart)	0	Mortality c-stat: [23]		X			
	Charlson comorbidity score [24]		Charlson = 0.704					
	Elixhauser comorbidity score [55]		Elixhauser = 0.793					
Social support	Modified Medical Outcomes Study Social Support (mMOS-SS)	11	Cronbach’s α = 0.88-.93 [56]		X			
Religion/spirituality	Self-reported extent of how spiritual/religious (5-pt Likert) and role play in decision-making.	4	Spirituality associated with quality of life. Religiosity associated with wanting all measures to extend life [57]		X			
Prior ACP experience	Prior ACP experiences (for example, Ever had to make life threatening medical decisions?”) [12]	5			X			
Major life changes	For example, “In the past 6 months, have you or someone close to you been faced with a serious medical problem or diagnosis?”	4						X
	Mediator variables^a^ (also measured as Outcome Variables)							
Baseline knowledge	Knowledge subscales of the ACP Engagement Survey.	6	Cronbach’s α = 0.84 (0.76-0.90), ICC = 0.70 (0.50-0.82) [15]		X			
Baseline self-efficacy	Self-efficacy subscales of the ACP Engagement Survey.	6	Cronbach’s α = 0.83 (0.75-0.89), ICC = 0.60 (0.41-0.76) [15]		X			
Baseline readiness	Readiness subscales of the ACP Engagement Survey.	10	Cronbach’s α = 0.92 (0.88-0.95), ICC = 0.60 (0.53-0.81) [15]		X			
Baseline barriers	Checkbox of 13 common barriers	13	Associated with ACP [25]		X			
Baseline attitudes	Processes of Change for ACP [16]	34	Responsive to an ACP intervention [15]		X			
Desired role in decision-making	Control Preference Scale (CPS) [58]	2	Correlation between preferred and actual role in decision-making [59–61]		X			X
	Primary Outcome Variables							
Full process of ACP	ACP Engagement Survey: Process Measures of knowledge, contemplation, self-efficacy, readiness	116	Process Measures: Cronbach’s α = 0.94 (0.91-0.96), ICC = 0.70 (0.54-0.82) [15]		X	X	X	X
	Action Measures: completion of advance directives, discussions		Action Measures: ICC = 0.87 (0.79-0.92) [15]					

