## Outcomes and Sample Size Calculations

### Primary outcome

The primary outcome is advance directive documentation in the medical record. This outcome was selected based on prior studies that have shown that advance directive interventions can increase documentation. A meta-analysis demonstrated a pooled effect size of 0.50 (95 % CI; 0.17-0.83) suggesting a positive effect associated with advance directive interventions [36]. One RCT of an ACP workbook in older Veterans also demonstrated an increase in living wills documented from 23 % in controls to 48 % in the intervention group (*P* < .001); and ACP notes from 24 % to 47 % (*P* < .001) [37]. Consistent with results from prior studies, our pilot study showed that a literacy appropriate advance directive doubled completion rates from baseline [12]. From SFVAMC administrative data, 11 % of the potential study sample had an advance directive in their medical record. We assume that after being included in the study, the control group may have an advance directive documentation rate of 15 %. If we assume doubling of the percent of ACP discussion notes between groups (what we consider clinically significant), a sample size of 350, or 175 in each arm, will afford us 92 % power with a two-tailed alpha of 0.05 to detect an elevation in rate of advance directive documentation from 15 % in controls to 30 % in the PREPARE group and 80 % power to detect a difference of 15 % in controls versus 27 % in the PREPARE group. After accounting for an estimated 15 % attrition rate, including death at 6 months (based on prior work) [12], our recruitment target is 410 Veterans or 205 in each arm.

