### Secondary outcomes

The secondary outcomes of this study include a comprehensive range of five specific ACP behaviors: 1) identification of a surrogate, 2) identification of values and goals, 3) choosing the level of leeway or flexibility in decision-making for the surrogate, 4) communicating this information with clinicians and surrogate decision-makers, and 5) documenting one’s wishes. We hypothesize that the scores from these ACP engagement items could be 50 % higher in the PREPARE group compared to the control group. Based on a pilot, the mean engagement scores for older outpatients were 30.7 points out of 57 ± SD of 10. Therefore, we expect a mean score as high as 40 points, a 10-point average difference between PREPARE and controls. However, even an increase of three points may represent a new action in any of the five domains. Using a two-tailed alpha of 0.05, 175 veterans in each randomization group will give us > 99.9 % power to detect a 10-point difference in engagement score, 96 % power to detect a four-point difference, and 80 % power to detect a three-point difference. A sample size of 350 will also allow us to assess each of the five domains of the preparation engagement survey separately as dichotomous variables, “action taken/no action taken”. If we assume a doubling of the percent of Veterans who “took action” within each of the five domains, using a two-tailed alpha of 0.05, we estimate that 175 veterans in each randomization group will give 92 % power to detect a doubling in the percent of Veterans who “took action” from 15 % (controls) to 30 % (PREPARE group) and 88 % power to detect a difference of 15 % versus 27 %. Taking into account an anticipated 15 % drop out as describe above, our anticipated 410 Veterans or 205 in each arm will provide us ample power to assess these outcomes.

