There have been a few logistic challenges to date. Although we attempt to schedule Veteran’s baseline appointment and randomization 1 to 3 weeks prior to their most proximate primary care appointment, this, at times, has been difficult to implement for various reasons. For example, some Veterans reschedule their baseline interview resulting in the intervention occurring within a few days before their clinic visit. Other Veterans or the clinic will cancel a primary care appointment after the baseline interview has occurred resulting in a time frame beyond the three-week ideal. We will adjust for these varying time frames from exposure to the intervention in our analyses. In addition, because the audio-recording occurs at the primary care visit and because several primary outcomes of the study would occur at the primary care visit, we decided to make the primary care visit the date from which all follow-up interviews would be calculated. Because follow-up of the 1-week, 3-month and 6-month interviews within defined time frames was proving challenging, we decided to allow a range of dates that were acceptable. For instance, if a primary care appointment is rescheduled is outside of the ideal 1-3 week window from the baseline interview and randomization, we will audio-record the primary care appointment up to 6 months after the baseline interview, but not after. For the one week follow-up interviews, the allowable Veteran interview range was changed from as early as 5 days from their primary care appointment to as late as 2 weeks prior to their 3-month follow-up; for the 3-month interview the range is from as early as 2.8 months from the primary care appointment to as late as 2 weeks before the 6-month interview; and for their 6-month interview, the ranges is from as early as 5.8 months from the primary care appointment to as late as 9 months from the appointment.

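### The primary outcome is stated in contradictory ways (record documentation, the self-reported survey, or both), and the 5% alpha and 92%/80% power apply only if record documentation is the sole primary

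*Protocol article*

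**What the plan says.** All of these statements stand in the current text of the protocol article.

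**Record documentation as the primary outcome**
- Primary outcome section: "The primary outcome is advance directive documentation in the medical record". The closing paragraph of the Background agrees in substance.
- Aims and primary hypotheses: the PREPARE arm is expected to show "increased rates of ACP documentation in their medical record (advance directives, clinicians notes, code status orders". The same section says that the sample size was calculated on this outcome and calls the survey hypotheses secondary.
- Abstract, Methods/Design: "The primary outcome is documentation of an advance directive and ACP discussions".

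**The survey as the primary outcome**
- Table 2 (Measures and data collection): the only entry under the primary heading is "ACP Engagement Survey: Process Measures of knowledge, contemplation, self-efficacy, readiness", together with the survey's action measures. No row covers documentation found in the record.

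**Both, or several**
- RCT efficacy analysis: "Our primary analyses will compare advance directive completion rates and change in engagement in the five ACP behaviors", using process scores and action scores. For the five behaviours it points the reader to the Primary outcome section, but they are set out in the next section, which begins: "The secondary outcomes of this study include a comprehensive range of five specific ACP behaviors".
- Discussion: the visit date was chosen as the anchor for follow-up partly because "several primary outcomes of the study would occur at the primary care visit".

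The Primary outcome and Secondary outcomes sections each calculate power at a two-tailed alpha of 0.05. Neither divides alpha or orders the tests.

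**The concern.** The outcome section, the measures table and the analysis section give three different answers to one question: which comparison decides whether PREPARE worked? A chart-based binary endpoint and a self-reported score can easily disagree in a trial of this kind. A website that models communication may move readiness scores without moving documentation, and the protocol's own theory section expects people to pass through such stages.

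Two things are at stake. First, if the joint statement in the RCT efficacy analysis section is followed and any one result is accepted, the chance of a false primary claim exceeds 5%. Secondly, with conflicting statements on file, the deciding outcome could be settled after the results are known, and each choice could be defended from some part of the text.

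The record outcome also has an unclear edge. It is not settled whether notes of ACP discussions count towards it, and this affects the control rate behind the sample size.

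**Working it through.** **Step 1. Reproduce the stated power.** Inputs from the Primary outcome section: 175 per arm, two-sided alpha 0.05, 15% in controls, and 30% or 27% with PREPARE. For the two-proportion test with pooled variance under the null:

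power = Φ[(d − z·SE0) / SE1], with SE0 = √(2·p̄·(1−p̄)/n) and SE1 = √((p1(1−p1) + p2(1−p2))/n)

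- 15% v 30%: p̄ = 0.225, SE0 = 0.0446, SE1 = 0.0439. (0.15 − 1.96 × 0.0446)/0.0439 = 1.42, so power is **92.3%** (stated 92%).
- 15% v 27%: p̄ = 0.21, SE0 = 0.0435, SE1 = 0.0431. (0.12 − 1.96 × 0.0435)/0.0431 = 0.80, so power is **79.0%** (stated 80%; the unpooled form gives 79.6%).

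The stated figures therefore belong to one identifiable test: record documentation, tested once at 0.05.

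**Step 2. Error rate if the joint primaries are each tested at 0.05 and any one suffices.** That success rule is an assumption, as the protocol states none. Count two tests (documentation, engagement) or three (documentation, process score, action score).

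- Two independent tests: 1 − 0.95² = **9.75%**.
- Three independent tests: 1 − 0.95³ = **14.3%**.
- Correlated tests (simulated multivariate normal statistics, assumed common correlation 0.3 to 0.8): about 7.8% to 9.5% for two and 9.8% to 13.6% for three.

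**Step 3. Price of keeping joint primaries with Bonferroni, 175 per arm.** Use the Step 1 formula with z for alpha/2 or alpha/3.

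- 15% v 30%: z = 2.241 gives (0.15 − 2.241 × 0.0446)/0.0439 = 1.14, so **87.2%**. z = 2.394 gives 0.98, so **83.7%**.
- 15% v 27%: 69.9% for two tests and 64.3% for three.
- Restoring 92% for 15% v 30% would take about 204 (two tests) or 222 (three tests) evaluable Veterans per arm. The plan expects 205 × 0.85 ≈ 174.

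**Step 4. Components of the record outcome, side by side.**

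- Abstract: directive and ACP discussions.
- Aims and primary hypotheses: directives, clinician notes and code status orders.
- Measures related to advance directive and ACP documentation: the study definition of an advance directive covers the VA and easy-to-read forms, living will, durable power of attorney, POLST, and other recorded wishes, exemplified by code status orders. Notes are not listed, although ACP discussions are mentioned as assessed alongside.
- Primary outcome section: the sentence giving the power assumes a doubling of ACP discussion notes but reports power for advance directive documentation, from an advance directive base rate (11%, taken to 15% for controls).

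Code status orders are thus covered by the study definition. What remains open is whether notes count.

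**The case against.** The strongest reply is that the intended primary is plain. The Aims section states one primary hypothesis, ties the sample size to it and labels the survey hypotheses secondary. The Primary outcome section gives alpha, sample size and power for the same comparison, and the figures reproduce. On this view the Table 2 heading and the phrase in the analysis section are loose drafting, and the plural in the Discussion is a narrative aside. Nowhere does the protocol say that any one of several primaries may succeed.

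Much of this stands. A reader might infer that the 5% alpha and the stated power belong to no test at all; the documents do not support that. The Discussion remark is weak evidence. The inflated error is conditional on a success rule that is not written down, and 14.3% is an upper figure, since process and action scores come from one survey.

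A reader might also infer that widening the record outcome to include notes necessarily costs power, for instance by using the 24% control rate for ACP notes in the cited Veteran trial and keeping a 12- or 15-point difference. That does not follow. The 24% is another trial's rate for notes alone. The Primary outcome section's own criterion of clinical significance is a doubling, and 24% v 48% at 175 per arm gives (0.24 − 1.96 × 0.0513)/0.0497 = 2.81, or 99.7% power. The direction depends on the effect assumption.

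The reply does not remove the contradiction. The section introducing Table 2 presents it as listing all measures assessed at multiple time points, and the record is reviewed at baseline and 6 months, yet it has no row there. The analysis section expressly includes the survey scores among the primary analyses. These are conflicting positive statements, not detail left to an analysis plan.

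**Conclusion.** The point holds as a contradiction about which outcome is primary. The 5% alpha and the 92%/80% power are sound for record documentation as the sole primary outcome, and only for that.

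If the joint reading were followed without adjustment and any result sufficed, the familywise error would be up to 9.75% (two tests) or 14.3% (three), reached under independence and lower with positive correlation. With Bonferroni, power for 15% v 30% would be 87.2% or 83.7%. These sizes rest on the assumed success rule, on counting two or three tests, and on 175 evaluable per arm.

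Whether notes count in the record outcome is a secondary ambiguity. It leaves the 15% control rate unsupported for a definition that includes notes, but the documents do not allow a power loss to be claimed.

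Confidence is high for the contradiction. The consequences are conditional, as stated.

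**What to change.** 1. Name documentation in the medical record as the single primary outcome, tested once at two-sided 0.05. Give one component list that says whether ACP discussion or clinician notes count.
2. In Table 2, add a row for the record outcome under the primary heading and move the ACP Engagement Survey to secondary.
3. In RCT efficacy analysis, limit the primary analysis to the record outcome, describe the engagement scores as secondary, and correct the cross-reference for the five behaviours.
4. Align the Abstract, the closing paragraph of the Background, Aims and primary hypotheses, the measures section on documentation, the Primary outcome section and the Discussion remark.
5. If notes are included, restate the control rate and power for that definition, under both a fixed absolute difference and a doubling. If they are not, the present calculation stands; remove the reference to notes from it.

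Declaring co-primaries with divided alpha would also resolve the conflict, but at the power cost shown in Step 3. The Trial status section reports that the 410 Veterans have already been recruited, so a larger sample is not part of the plan.

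The cost is wording in the protocol and any analysis plan, with no new data. The change should be dated before outcomes are compared by arm.

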#### Measures related to advance directive and ACP documentation

Standard ACP is measured by the completion of advance directives in the VA electronic medical record. We will assess baseline advance directive completion rates and the date the advance directive was signed as well as ACP discussions. At 6 months (date of the last follow-up interview), we reassess the advance directive completion rate and the date it was signed to determine length of time from study enrollment to documentation. An advance directive for the purposes of this study includes the VA or easy-to-read advance directive, a living will, a durable power of attorney for health care document (DPOAHC), a Physicians Orders of Life Sustaining Treatment form, or other documentation of the patient’s wishes for medical care (code status, such as full code or do not resuscitate or do not intubate orders by a physician).

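### The self-reported ACP Engagement Survey is secondary in the hypotheses and outcome sections but primary in Table 2 and the analysis section, so the result that decides efficacy is not fixed consistently

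*Protocol article*

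**What the plan says.** **Documentation as primary.** The Primary outcome section states: "The primary outcome is advance directive documentation in the medical record". The abstract is slightly wider: "The primary outcome is documentation of an advance directive and ACP discussions". The Background names advance directive completion. The primary hypothesis covers advance directives, clinicians' notes and code status orders, and says that the sample size was calculated on this outcome.

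**Engagement as secondary.** The hypotheses section makes process measures and further ACP actions secondary hypotheses. The Secondary outcomes section agrees: "The secondary outcomes of this study include a comprehensive range of five specific ACP behaviors".

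**Engagement as primary.** Three places depart from this:

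- Table 2, under "Primary Outcome Variables", has one entry, the full process of ACP, measured by "ACP Engagement Survey: Process Measures of knowledge, contemplation, self-efficacy, readiness" together with the survey's Action Measures. The Measures section says that engagement is self-reported. Chart documentation has no row of its own.
- The RCT efficacy analysis section says "Our primary analyses will compare advance directive completion rates and change in engagement in the five ACP behaviors (see Primary outcome section". The five behaviors are listed in the Secondary outcomes section, not in the section cited.
- The Discussion, explaining why follow-up is counted from the clinic visit, says "because several primary outcomes of the study would occur at the primary care visit".

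**The concern.** One outcome has opposite status in different parts of the current text. A team following the Primary outcome section would judge the trial on chart documentation. A team following Table 2 would judge it on a self-reported survey. A team following the analysis section would have both among its primary analyses, with engagement scored in two ways (process and action). These can disagree: the survey may move while the chart does not, and the report could then say that the primary outcome was met or not met depending on the place cited. The hypotheses section also describes the secondary outcomes as no less clinically meaningful than the primary one, so a claim built on the survey is a realistic prospect. Each outcome is given the full 5% in its own power calculation, so nothing in the article holds the overall error at 5% if more than one counts as primary.

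**Working it through.** **1. Where each outcome stands**

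| Place in the article | Chart documentation | Engagement survey |
|---|---|---|
| Abstract, Background | primary | among other or secondary outcomes |
| Aims and primary hypotheses | primary; basis of the sample size | secondary |
| Table 2 | no row | only primary entry |
| Primary outcome | primary | not listed |
| Secondary outcomes | - | secondary |
| RCT efficacy analysis | primary analyses | primary analyses |
| Discussion | plural primary outcomes, not named | plural primary outcomes, not named |

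**2. The plan's own figures**

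Inputs from the Primary outcome section: 175 analysed per arm, 15% v 30%, two-sided 0.05. With p̄ = 0.225:

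- SE under no difference = √(0.225 × 0.775 × 2/175) = 0.04464
- SE under the alternative = √((0.15 × 0.85 + 0.30 × 0.70)/175) = 0.04392
- Power = Φ((0.15 − 1.96 × 0.04464)/0.04392) = Φ(1.423) = 92.3%. The article states 92%.

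The same formula gives 79.0% for 15% v 27%. The Primary outcome section states 80%.

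For the engagement score (SD 10, Secondary outcomes section), SE = 10 × √(2/175) = 1.069:

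- 3 points: Φ(3/1.069 − 1.96) = 80.1%. The article states 80%.
- 4 points: 96.3%. The article states 96%.

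Each calculation therefore uses the whole two-sided 5% for one outcome at a time.

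**3. False-positive chance if any one of k primary tests could succeed**

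If the tests are independent, the chance is 1 − 0.95^k:

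- k = 2 (documentation, engagement): 1 − 0.9025 = 9.75%
- k = 3 (documentation, process score, action score): 1 − 0.857375 = 14.3%

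The outcomes are probably positively correlated, since the survey's Action Measures include self-reported advance directive completion. The article gives no correlation, so these are assumed. Simulated equicorrelated normal statistics (2,000,000 draws, two-sided 0.05) give:

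| Assumed correlation | k = 2 | k = 3 |
|---|---|---|
| 0.3 | 9.5% | 13.6% |
| 0.5 | 9.1% | 12.5% |
| 0.7 | 8.4% | 10.9% |
| 0.8 | 7.8% | 9.8% |

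**4. What keeping more than one primary would cost**

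With an equal split of alpha, as an illustration:

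- Two primaries at 2.5% each: power for 15% v 30% = Φ((0.15 − 2.241 × 0.04464)/0.04392) = 87.2%. Keeping 92% needs about 204 analysed per arm, or 204/0.85 = 240 recruited per arm at the article's 15% attrition. The target is 205 recruited per arm.
- Three primaries at 1.67% each: power 83.7%, or about 222 analysed per arm.

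With documentation as the only primary outcome, the error stays at 5% and the power at 92%.

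**The case against.** The strongest reply is that a careful reader can tell what was meant. Documentation is named as primary in four places, including the sample size section. On this view, what remains is a misplaced table heading, a wrong cross-reference and a loose phrase in a paragraph on logistics. It stands that documentation is the dominant statement, and this is why the repair is simple. It does not remove the conflict: the table that defines the measures and the section that defines the analysis both depart from it.

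Some stronger readings are tempting, and the article does not support them:

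- **One positive test is enough.** No sentence says so. A decision rule may stand in the analysis plan, which is not shown, and its absence from an article is no fault. If both outcomes had to succeed, the error would not exceed 5% and the cost would be power instead. Any such rule must still start from one list of primary outcomes.
- **The 92% power and 5% alpha belong to the chart outcome alone.** The Secondary outcomes section states the same alpha, and 92% for 15% v 30%, for the dichotomised survey domains.
- **Before 6 months, directive completion can come only from self-report.** At the 6-month chart review, "we reassess the advance directive completion rate and the date it was signed", so earlier status can be derived for advance directives. The visit times in the analysis sentence may also attach only to the engagement scores.
- **Every score is tested separately at every visit, with a much larger inflation.** The analysis section plans longitudinal mixed models. It does not state separate tests at each visit.
- **The survey is answered unblinded.** The Blinding section says that participants are blinded to group assignment and told only that they will review one of two guides. It also keeps the baseline interviewer from that participant's follow-up interviews. One may doubt how well this works, but it is the stated design.

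**Conclusion.** The article is wrong as written: engagement is secondary in the hypotheses and the Secondary outcomes section, but primary in Table 2 and the analysis section. This is visible in the current text and does not depend on any document that is not shown. The size is conditional. If documentation and engagement both counted as primary and either alone sufficed, the false-positive chance would be about 8-10% for two tests or 10-14% for three, instead of 5%. These ranges rest on that inferred rule and on assumed correlations from 0 to 0.8. Whatever the figure, the article should show one primary outcome throughout before the data are analysed.

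**What to change.** 1. **Table 2:** move the ACP Engagement Survey to the secondary outcomes. Add medical-record documentation, assessed at baseline and 6 months, as the only primary outcome. Give it one definition. At present the scope differs between the abstract (directives and discussions), the Background and the Primary outcome section (directives), the hypotheses (directives, notes and code status orders) and the documentation measures section (a broad list of forms and orders).
2. **RCT efficacy analysis:** state that the primary analysis compares medical-record documentation at 6 months at two-sided 0.05, and that process and action engagement scores are secondary. Point the cross-reference for the five behaviors to the Secondary outcomes section. Comparisons of directive completion at 1 week and 3 months may stay as secondary, using the recorded signing dates.
3. **Discussion:** replace the reference to several primary outcomes with one to several outcomes.

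The cost is wording in one table and two paragraphs, plus agreement on the definition. Recruitment of the 410 Veterans is complete, and neither the sample size nor the 92% power changes. The price is that an efficacy claim can no longer rest on the survey alone.
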